## **14.6 RANDOM ASSIGNMENT**

The randomization scheme will be generated and maintained by [name] at Boston University. Women will be randomized to one of the two arms of Segment B in a 1:1 ratio using block randomization (5 blocks of 6 women). Since some participants may become non-evaluable prior to the adequate outcome or safety assessments (see Section 14.2) these participants will need to be replaced in the study. This could potentially lead to an imbalance in the treatment allocation. To handle this situation, after each block of women is randomized, it

will be noted when any are removed from the study because of being non-evaluable. If equal numbers of placebo and active drug recipients are being removed then the randomization plan as described above will retain balance in group allocation, and an additional block of women (with size equal to the total number of non-evaluable women) will be randomized. However, if an unequal number of participants from one group are removed because they become non-evaluable (e.g., 2 women in the placebo group vs. 1 woman in the active film group), then one of the remaining blocks of non-randomized women will be altered to include additional participants from the group had more participants removed (i.e., the last block will be constructed to have 9 women (rather than 6) with 5 to be randomized to the film only group and 4 to be randomized to the film plus drug group in this example).

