## 10.3 ADMINISTRATION

A study clinician will manually insert the MB66 film in the clinic for Segment A participants, and Segment B participants will self-administer their first dose of study film in clinic in the presence of the study clinician (to assure themselves and study staff of their ability to insert the film), and then self-administer doses 2-7 at home. Segment B participants will take home their remaining doses in a vial capped with a Medication Event Monitoring System (MEMS) cap, to provide objective data about adherence with and timing of at home dosing, (each opening of the MEMS cap will be electronically recorded for time and date, with data downloaded at Visit 4). An extra dose of study film will be available for each Segment A participant in case of an

initially unsuccessful insertion, and three extra doses provided for each Segment B participant in case of unsuccessful insertion in clinic, at home, or for the possibility of delaying Visit 4 to Day 8 instead of Day 7. *(While the intended duration of exposure for Segment B participants is 7 days, participants who are only able to reschedule Visit 4 on Day 8 post MB66 administration will be allowed to do so. For that group, the total dosing will be 8 days rather than 7. Every effort will be made to bring participants back on Day 7 so as to minimize variation in product exposure. Participants will only be enrolled if they indicate their availability to return on Day 7, but if a scheduling conflict should arise post enrollment, they will be allowed to return to the clinic for Visit 4 on Day 8 after administering an additional dose of film on day 7.)*

For Segment A participants the study will be open label (unmasked). For Segment B, the film identity (active or placebo) will be randomly assigned and assignment will be single blinded (study film identity will be masked to the participants) Reliable blinding of study staff will not be feasible due to the non-identical degree of film translucency of the active and placebo films.

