#### 11.1.2.3 Segment B, Visit 2: Enrollment

Subjects who meet the inclusion and exclusion criteria following the Screening Visit may schedule an Enrollment Visit. Care will be taken to attempt scheduling the Enrollment Visit at a time when the participant is not expecting to be menstruating or anticipating her menses within 16 days.

Before performing any study procedures, an enrollment eligibility checklist will confirm that the participant meets criteria including laboratory test results and history. The participant will undergo a brief physical exam and pelvic examination. Pelvic specimens as described below will be collected via speculum and the study staff will assess for bleeding and epithelial lesions. If no bleeding or other exclusionary findings are evident, the participant will then be randomized to study product and assigned a Participant ID Number. The act of randomization is considered the act of enrollment for Segment B.

Subjects with active vaginal bleeding at the Enrollment Visit will not be randomized/enrolled at that time, but may be rescheduled for another Enrollment Visit. If vaginal bleeding does not resolve during the screening window period, and the subject expresses interest in enrollment for the study and no other exclusionary findings are detected, she may be allowed to rescreen.

It is anticipated that the participants' familiarity with vaginal products will vary and that very few of the women will have had any experience with vaginal film insertion. To ensure consistency of application, participants will undergo a standardized training on the study product application after randomization. The training will include viewing a brief video (instructional video demonstrating the handling of VCF film (see description and link under Enrollment Visit for Segment A), a marketed vaginal contraceptive film with similar size and consistency to the MB66 study films). Participants will then practice insertions using VCF film, first into a transparent pelvic model, and then into a silicone vaginal model. The clinic staff will be immediately available to answer any questions or address any concerns. Participants will then insert their first dose of Study Film vaginally, in the presence of the study clinician, who will assess the participant's competence in the film insertion procedure (ability to insert fully without visible film at the introitus or on the fingers), and provide additional guidance as needed.

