## **14.5 BLINDING**

Segment A will be open label since all participants will receive active film. Segment B participants will be blinded to assignment of active drug versus placebo. Because the active and placebo films are not identical in appearance, study staff cannot reliably be blinded to assignment, and hence we characterize Segment B as “single blind”. However, we will attempt to maintain blinding to assignment during laboratory testing, and among data recording and data analysis teams.

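### A fixed block size of 6, printed in the protocol, lets site staff who cannot reliably be blinded foresee about a quarter of Segment B assignments

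*Protocol*

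**What the plan says.** **Allocation.** Protocol Section 14.6: "Women will be randomized to one of the two arms of Segment B in a 1:1 ratio", "using block randomization (5 blocks of 6 women". The list is generated and held off site.

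**Replacement.** The same section publishes how blocks change after drop-out. If losses are equal between arms, "an additional block of women (with size equal to the total number of non-evaluable women) will be randomized". If they are unequal, a block still to come is altered. In the worked example two placebo women and one active woman are lost, and "the last block will be constructed to have 9 women (rather than 6) with 5 to be randomized to the film only group", leaving 4 for the active film.

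**Blinding.** Section 10.3: "Reliable blinding of study staff will not be feasible due to the non-identical degree of film translucency". Section 14.5 repeats that "study staff cannot reliably be blinded to assignment" and calls Segment B single blind, with an attempt to keep laboratory and data teams blinded.

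**What staff see.** Section 11.1.2.3: "Participants will then insert their first dose of Study Film vaginally, in the presence of the study clinician". Section 8.6 names one site, so the same clinic sees every assignment and every drop-out.

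**Safeguards stated.** Besides the off-site list, pharmacy records are closed to other research staff (Section 10.6), and randomization follows the eligibility check (Section 11.1.2.3).

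**The concern.** Permuted blocks conceal the next assignment only if the site does not know either the block size or what has already been allocated. Here the size is in a document the site holds, and past allocations can largely be read from the films. Once one arm is used up within a block, the rest of that block is known.

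The stated safeguards do not close this route. The off-site list and the closed pharmacy records hide future entries, but staff can deduce some of those entries from past films and the block size.

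Enrolment leaves room for judgement. Menstrual irregularity, HIV risk and general suitability are decided by the principal investigator or investigators (Section 9.3, items 11, 13 and 25). Women with bleeding at the Enrollment Visit may be rescheduled or rescreened (Section 11.1.2.3). Staff who foresee the next assignment could, even without intent, influence which woman receives it. With 15 women per arm, moving one or two could shift an active-placebo contrast. Those contrasts bear on the first hypothesis in Section 6.3 and on the microbial and immune-mediator objectives in Section 7.3.

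**Working it through.** **Inputs.** Five blocks of 6 at 1:1, so 3 active and 3 placebo per block (Section 14.6); 15 evaluable women per arm (Section 14.2). Assumption: staff know the block size and all earlier assignments.

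**The plan's own figures.** 5 × 6 = 30 women, 15 per arm. Rebuilt block: (3 + 2) placebo + (3 + 1) active = 5 + 4 = 9. Both reproduce.

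**Definitions.** An assignment is certain when one arm is already exhausted in the block. The best guess is always the arm with more places left, or a coin toss when the two are equal. For a block with *a* and *b* places, the expected number certain is a/(b+1) + b/(a+1). For *m* per arm, the expected number of correct guesses is m + (2^(2m)/C(2m,m) − 1)/2. Full enumeration gives the same values for the equal-arm blocks below. The guessing figure for 5:4 comes from enumerating its 126 orders.

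- Block of 6 (3:3): certain 3/4 + 3/4 = 1.5, which is 25%. Correct guesses 3 + (64/20 − 1)/2 = 4.1, which is 68.3%.
- Five such blocks: 5 × 1.5 = 7.5 of 30 certain; 5 × 4.1 = 20.5 of 30 guessed, against 15 by chance.
- Replacement block of 2 (1:1): certain 1/2 + 1/2 = 1, which is 50%. Correct guesses 1 + (4/2 − 1)/2 = 1.5, which is 75%.
- Replacement block of 4 (2:2): certain 2/3 + 2/3 = 1.33, which is 33%. Correct guesses 2 + (16/6 − 1)/2 = 2.83, which is 70.8%.
- Rebuilt block of 9 (5:4): certain 5/5 + 4/6 = 1.67, which is 18.5%. Correct guesses 6.03, which is 67.0%. The first place is placebo with probability 5/9.

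Small replacement blocks are the realistic case: Section 9.7 expects 43 − 38 = 5 non-evaluable women in the whole trial.

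**Effect of hiding and varying the block size.** In simulated lists of 30, with staff guessing only from the running imbalance, the correct share is 68.8% for sizes 4/6, 67.5% for 4/6/8 and 69.8% for 2/4/6, against 68.3% for a fixed 6. Staff can no longer deduce an assignment with certainty, provided the set of possible sizes is also withheld.

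**Why 15 evaluable per arm must be kept.** Section 14.7.2 counts a 30% rate as ruled out when the one-sided 95% Clopper-Pearson upper limit is below 30%, which it says happens with zero or one event in 15. For one event the limit solves (1 − p)^n + n·p·(1 − p)^(n−1) = 0.05:

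| Evaluable in arm | Upper limit, 1 event |
|---|---|
| 15 | 27.9% (the plan's figure) |
| 14 | 29.7% |
| 13 | 31.6% |

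At 13 the plan's rule fails with one event.

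**The case against.** The strongest reply is about consequence. The Segment B primary analysis is an exact interval within each arm. Section 14.7.2 labels the Fisher comparison exploratory, and Section 14.7.4 says active-placebo comparisons are not the primary aim. Predictable allocation threatens mainly those contrasts. This stands, and it limits the weight of the point.

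The text also says only that staff cannot *reliably* be blinded, and Section 10.4 describes the placebo as similar but more transparent. That staff learn every assignment, or that those who see the films also decide enrolment, is a strong inference from one site and the Visit 2 procedures. It is not a stated fact, so the 25% and 68% are what full knowledge would allow.

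Three stronger readings are tempting, and the documents do not support them:

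- *Rebuilding blocks makes allocation more predictable.* The protocol's own block of 9 is slightly less predictable than a block of 6 (18.5% against 25% certain; 67.0% against 68.3% guessed). Its weakness is a tilt that staff can work out from the published rule. Only the small replacement blocks are more predictable.
- *The extra block could contain one arm only.* Section 14.6 describes the extra block for equal losses. Unequal losses alter a block still to come.
- *Allocation depends on outcome.* Evaluability rests on attendance and recorded product use (Section 14.2), and a woman who becomes non-evaluable after an adverse event on study stays in the primary analysis. A Grade 3 or 4 event ends product use (Section 13.6) and could make a woman non-evaluable, so any link is at most indirect.

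**Conclusion.** The point holds as a weakness of allocation concealment that is cheap to remove. With the printed block size and known history, up to 7.5 of 30 assignments are certain in advance and 20.5 of 30 can be guessed. In a replacement block of 2 the second assignment is always known. The figures assume that staff identify each film correctly and use the block size. The risk is selection bias in exploratory active-placebo contrasts. A reader might infer that the primary conclusion is compromised, but the per-arm interval does not rest on comparing the arms. The change should be made before Segment B opens, and it should not give up 15 evaluable women per arm.

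**What to change.** - Before Segment B opens, have the off-site statistician prepare an over-length list with randomly varied block sizes.
- Move the block sizes and the replacement rule out of the site protocol into a restricted randomization document. Section 14.6 then need only state 1:1 blocked allocation with sizes withheld from the site, and replacement of non-evaluable women.
- Keep replacing until each arm has 15 evaluable women. The off-site statistician builds any extra or altered block without telling the site its size or ratio.
- Use the restricted document to settle two loose ends in Section 14.6: whether the altered block is the last one or any remaining one, and what happens when unequal losses appear only after the last block.

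**Cost.** A new list, one short restricted document and an edited paragraph. One or two extra women may be enrolled. Average guessing accuracy stays near 67-70%, so the benefit is that no assignment can be known for certain. A single long permuted list, or a ban on rebuilding blocks, is not advised unless 15 evaluable per arm is still secured, because an arm ending at 13 with one event would miss the 30% criterion.

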## **14.7 DATA MONITORING AND ANALYSIS**

### **14.7.1 Data Monitoring**

This clinical trial will be conducted in compliance with the protocol, GCP guidelines, and applicable regulatory requirements. All research charts are maintained in locked files in a locked room.

Some case report forms will be used as source documents, first point of data entry for this protocol. The case report forms will be photocopied and mailed to the data management group after all identifying information other than the participant ID number has been removed. Study data management staff will manually review the forms for completeness and accuracy. If there are any responses that are incomplete or unclear, the staff person will speak or email with the clinician in question as soon as possible to resolve the problem. If necessary, the study staff member who collected the data will mark out the previous response (not erase or obliterate it), fill in the new response, and date and initial the change. Once the source documents are ready for computer entry, data management staff will enter data into a data entry system.

### **14.7.2 Primary Endpoint Analysis**

The primary endpoint of the study is to determine the incidences of Grade 2 or higher Adverse Events deemed related to study product. Adverse Events will be measured using the definitions provided in the Division of AIDS (DAIDS) Table for Grading the Severity of Adult and Pediatric Adverse Events, Version 2.0. [November 2014], and the Female Genital Grading Table for Use in Microbicide Studies (Addendum 1 to the DAIDS Table for Grading Adult and Pediatric Adverse Events, Version 1.0, November 2007 [Clarification dated August 2009]). For Segment A, the primary analysis will be to determine whether any Grade 2 or higher Adverse events deemed related to study product occur. If Grade 2 or higher AEs do occur, the PSRT will determine whether advancement from the first to second group of Segment A participants should be allowed, and whether advancement from Segment A to Segment B should be allowed. This determination will be made based on the number, type, and product relatedness of the AEs observed.

For Segment B, the primary analysis of the primary endpoint will be conducted as follows. First, the incidence rate and one-sided 95% Clopper-Pearson (exact) binomial confidence intervals of

AE2's will be estimated for each group. The focus of these analyses will be to determine whether a 30% AE2 rate can be ruled out based on the data collected in the study. This will be shown if the upper bound of the 1-sided 95% Clopper Pearson (exact) binomial confidence interval is less than 30% which will occur if zero or one participant out of the 15 enrolled (in each arm) have an AE2. In addition, an exploratory comparison between the two groups in Segment B (active and vehicle) will be performed using a Fisher's Exact test to determine whether the number of participants with Grade 2 or higher AEs are different between groups. In addition to estimating the rate of Grade 2 (or higher) AE's in Segment B alone, estimates of combined Grade 2 or higher AEs rates can be derived by pooling the participants from Segment A and Segment B. In addition, Segment A participants (n=8) can be pooled with the participants from Segment B, allowing for Grade 2 or higher AEs estimates to be made using n=23 participants. One-sided 95% Clopper-Pearson (exact) binomial confidence intervals will be estimated for these AE2 rates. For the analyses with n=23 participants, the confidence intervals will have an upper bound of 29.4% if 2 (or fewer) participants have an Grade 2 or higher AEs. These analyses will provide supportive data to the primary endpoint analysis that is based on the Segment B (n=15) participants only. Additional detail of the statistical analyses will be provided in a separate statistical analysis plan (SAP), which will be prepared and signed off prior to completion of the study.

#### **14.7.3 Secondary Endpoint Analysis**

Summary statistics of frequencies, percentages, and 95% confidence intervals will be provided for categorical data. Means, standard deviations, medians, ranges and 95% confidence intervals will be provided for continuous data. Methods for the analyses of the secondary endpoints are described below. This Pre-Phase I study may not have an adequate sample size to detect significant differences within or between treatment arms.

In general, for continuous measures that are collected at multiple time points (vaginal and systemic antibody levels), repeated measures mixed models will be fit that allow the individual women to be considered as random effects in the models. Whenever possible the actual time of the measurement will be recorded during the study and the actual time interval between measures (i.e. number of hours between measures) can be considered in the repeated measures mixed models for accounting for time. This will allow for potentially a more sensitive analysis to the impact of time between measures to take place since there may be some variability among participants in the timing of the assessments. These models will be exploratory, but will allow longitudinal comparisons to be made both within treatment group and between treatment groups. For categorical or binary outcomes measured at multiple time points (film dissolution) a generalized estimating equations (GEE) approach will be used to compare participants within and between groups. As stated above, these analyses will be considered as primarily exploratory since there will be a limited sample size. If measures are taken only at one post randomization time point then we can compare groups using 2-sample t-tests (for continuous variables) and Fisher's exact tests (for categorical variables).

If the continuous data collected does not follow a normal distribution then appropriate transformations (i.e. log transformation) will be considered and if these do not fix the problem then non-parametric approaches will be considered (i.e. Kruskal Wallis tests).

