### **8.4.2 Segment B:**

Randomization will be 1:1 amongst the two groups of 15 evaluable participants each:

- Segment B Study Arm 1: 1 MB66 film
- Segment B Study Arm 2: 1 Vehicle control placebo film

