| Physical Exam                                                                                                       | Vital signs (temperature, blood pressure, heart rate)
Focused physical exam                                                                                                                                                                                                    |
| Pelvic Exam                                                                                                         | Gynecologic exam including visual inspection of external genitalia and speculum exam
Vaginal smear for Gram stain
Vaginal swab for pH
Vaginal swab for wet prep Δ
Pre-dose CVF via Tear Flo sampling (cervical os, ectocervix, mid vagina, distal vagina*) |
| Film dosing                                                                                                         | Clinician digital insertion of assigned film dose                                                                                                                                                                                                                                 |
| Post dose vaginal PK                                                                                                | 1 hour and 4 hour post dose Tear Flo MAb levels (cervical os, ectocervix, mid vagina, distal vagina), and visual assessment of degree of film dissolution                                                                                                                         |
| Δ If clinically indicated
* One sample at each site, at this visit and at all other Tear Flo sampling visits |                                                                                                                                                                                                                                                                                   |

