| Physical Exam                 | Focused physical exam
Vital signs (temperature, blood pressure, heart rate)                                                                                                                                                                                                                                                                                    |
| Pelvic                        | Gynecologic exam including visual inspection of external genitalia and speculum exam
Vaginal swab for pH
Vaginal swab for Gram stain
Vaginal swab for microbiome PCR
CVF via Tear Flo MAb levels (cervical os, ectocervix, mid vagina, distal vagina), and visual assessment of degree of film dissolution
Vaginal swabs for wet prep † |
| CVL                           | Anti-viral activity, MAb levels, and immune mediators                                                                                                                                                                                                                                                                                                             |
| Δ If clinically indicated |                                                                                                                                                                                                                                                                                                                                                                   |

#### 11.1.2.7 Segment B, Visit 5: Exit Visit, Day 14

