#### **14.4.2 Secondary Endpoints: Pharmacokinetics (PK)**

##### Distribution and Persistence of MB66 MAbs in CVF

The vaginal distribution and persistence of MB66 MAbs, VRC01-N and HSV8-N, will be determined by ELISAs carried out on vaginal fluid collected via Tear Flo strips. The fluid will be collected from different regions of the vagina and at different times after administration.

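### Putting the antibody-free placebo arm into the antibody-level mixed model can understate the error of the MB66 single-versus-repeat-dose contrast (about 12–17% false positives at nominal 5%)

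*Protocol*

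**What the plan says.** Section 14.7.3 covers continuous measures taken repeatedly and names vaginal and systemic antibody levels as the case in point. For these, "repeated measures mixed models will be fit that allow the individual women to be considered as random effects in the models". The models "will allow longitudinal comparisons to be made both within treatment group and between treatment groups". The section also states that "these analyses will be considered as primarily exploratory since there will be a limited sample size". Section 14.7.2 promises a separate SAP with further detail; that SAP is not at hand.

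For Segment B, "Randomization will be 1:1 amongst the two groups of 15 evaluable participants each". Section 10.4 describes the placebo film as the same excipients without the antibodies. Table 20 gives both arms the same Tear Flo and serum sampling.

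On vaginal sampling, section 14.4.2 says "The fluid will be collected from different regions of the vagina and at different times after administration". The visit tables list four sites: cervical os, ectocervix, mid vagina and distal vagina. The footnote to Table 7 adds "One sample at each site, at this visit and at all other Tear Flo sampling visits".

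Hypothesis 3 in section 6.3 is that daily use improves antibody distribution and lengthens residence time relative to a single film. Section 11.1.2.6 times the Visit 4 sample about 24 hours after the last dose, which matches the Day 1 sample taken 24 hours after the first dose.

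**The concern.** A model that compares antibody levels between arms has to contain the placebo women. They should have VRC01-N values at the assay floor. For HSV8-N, section 6.2.2 expects vaginal background generally below 1 µg/mL, against about 100 µg/mL regarded as relevant to protection. Stable differences by HSV serostatus would go into the woman effect, so little residual spread should remain in this arm. A log transformation does not help, because a constant stays constant.

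With one residual variance for both arms, the model averages the real visit-to-visit variation of MB66 women with almost none from an equally large placebo arm. The average is then used as the error for changes over time within the MB66 arm. The comparison most exposed is Day 1 against Visit 4 in MB66 women, the natural within-woman look at repeat dosing. Its p-value would be too small and its interval too narrow. The active-versus-placebo test itself says little more than that the drug was given.

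A second, less definite issue concerns the four sites. Samples from one visit share that visit's film, fluid and speculum procedure, and a woman effect does not describe this correlation.

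**Working it through.** The protocol states no variance component, power or error rate for this model, so there is no figure of its own to reproduce.

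**Inputs.** From the protocol: 15 evaluable women per arm, four sites sampled once each per visit, no antibody in the placebo film. Assumed: two-sided 5% (the protocol gives a level only for the Fisher test), one residual variance, and no true change between Day 1 and Visit 4. Let f be the placebo residual SD divided by the active residual SD.

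**Step 1: site-averaged data, closed form.** With one value per woman and visit and a woman intercept, the Visit 4 minus Day 1 difference in the active arm has true variance 2σ²/15, where σ² is the active residual variance. The two arms contribute equal residual degrees of freedom, so the pooled residual variance has expectation σ²(1 + f²)/2. The standard error is therefore multiplied by √((1 + f²)/2), and the large-sample false-positive rate is 2[1 − Φ(1.96·√((1 + f²)/2))].

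- f = 0: variance factor 0.5; 1.96 × 0.7071 = 1.386; rate 16.6%.
- f = 0.25: factor 0.531; 1.96 × 0.7289 = 1.429; rate 15.3%.
- f = 0.5: factor 0.625; 1.96 × 0.7906 = 1.550; rate 12.1%.
- f = 1: factor 1; rate 5.0%.

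A nominal 95% interval would thus be 0.71 times (f = 0) to 0.79 times (f = 0.5) its proper width.

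**Step 2: the same by simulation.** Four post-dose occasions (1, 4 and 24 hours, and Visit 4), t reference, 8,000 runs per cell. Degrees of freedom are 14 × 3 = 42 for one arm and 84 for two.

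| Data in the model | False-positive rate |
|---|---|
| Active arm only | 4.9% |
| With placebo, f = 0 | 16.7% |
| With placebo, f = 0.25 | 16.1% |
| With placebo, f = 0.5 | 12.4% |
| With placebo, f = 1 | 5.2% |

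At 16.7% the simulation standard error is √(0.167 × 0.833/8000) = 0.4 percentage points.

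**Step 3: four sites as separate rows, woman intercept only, Day 1 and Visit 4.** The columns give the assumed ratio of woman-by-visit variance to residual variance.

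| Setting | 0 | 0.1 | 0.25 | 0.5 | 1 |
|---|---|---|---|---|---|
| Active only, no lasting woman-by-site variance | 5.0% | 9.1% | 13.5% | 19.4% | 27.9% |
| Active only, woman-by-site variance equal to residual | 0.9% | 2.3% | 5.1% | 9.7% | 16.9% |
| With placebo at f = 0, no woman-by-site variance | 16.8% | 23.0% | 29.6% | 37.0% | 43.9% |
| With placebo at f = 0, woman-by-site variance equal to residual | 6.1% | 10.3% | 16.6% | 24.7% | 33.8% |

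The second row shows that the error can also be overstated. When a woman's sites differ consistently over visits, that variation is left in the residual although it cancels from the time contrast.

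**Step 4: a correct reference.** Averaging the four sites per visit and comparing Day 1 with Visit 4 by a paired test in the active arm gives 4.8% to 5.1% at every variance ratio tried.

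**The case against.** The strongest reply is that the harmful model is not written down. Section 14.7.3 speaks in general terms. It does not say that woman is the sole random effect, that sites enter as separate rows, or that the arms share a residual variance. Its within-group comparisons could come from arm-specific fits. Covariance structure and unit of analysis usually belong in the SAP, which section 14.7.2 promises. The models are labelled exploratory, no decision rule hangs on them, and hypothesis 3 is not tied by name to the Day 1 versus Visit 4 contrast.

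Most of this stands, and it largely settles the site issue, which is a matter of specification. It does not remove the placebo issue. The between-group comparison is stated, it requires placebo data, and a single residual variance is what the ordinary model supplies unless someone chooses otherwise. An exploratory label limits what is claimed from a p-value; it does not correct a standard error.

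A reader might infer that the protocol fixes an error term that is always too small, with false positives at least three times nominal. The documents do not support that. Inflation falls below threefold when placebo values vary appreciably (12.4% at f = 0.5) and can be near nil when sites differ persistently within women (6.1% even with placebo at the floor). With site rows in the active arm alone, the test can be conservative (0.9%). The site issue also does not reach serum, for which there is one sample per visit.

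**Conclusion.** The point holds as a low-cost improvement to a secondary, exploratory analysis. Following the stated between-group model in its usual form could give the MB66 single-versus-repeat-dose contrast a false-positive rate of about 12% to 17% at nominal 5%, with site-averaged data. This rests on three assumptions: a common residual variance, placebo residual SD between zero and half of the active SD, and 15 women per arm. If placebo values varied as much as active values, there would be no inflation from this source.

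The treatment of the four sites is an open specification that can push the error either way. Its direction and size depend on variance components the protocol does not give. The primary safety analysis is unaffected.

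**What to change.** In section 14.7.3, state that time and repeat-dose contrasts of antibody levels are estimated in MB66 recipients only, or in a model with arm-specific residual variances. Report placebo as the number and percentage of women with quantifiable values at each visit.

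For vaginal samples, use the per-visit mean across the four sites for time contrasts. Alternatively, include site as a fixed effect with random effects for woman, woman-by-visit and, if the data support it, woman-by-site.

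One caution applies to the active-only model. Pre-dose and Day 14 values in MB66 women may also lie near the floor, so a single residual variance over all visits could still misstate the error. A paired Day 1 versus Visit 4 comparison of site means avoids this.

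The cost is a few sentences and slightly different model code. Intervals will be wider. Visits, samples and sample size do not change, and no information on MB66 levels is lost.
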